### Registry study

There will be two analysis populations including 1) an Effectiveness Population which consists of all enrolled patients who will be matched by propensity score quintiles, all of whom have received at least 3 months of therapy per SOC without evidence of disease progression, and 2) a Safety Population which consists of all enrolled patients with the cohort assignment based on the actual treatment received.

For the primary efficacy endpoint, the null hypothesis for OS is stated as H_0_: S_soc_ = S_IRE_ and the alternative hypothesis is H_1_: S_soc_ ≠ S_IRE_, where S_soc_ is the median OS time for the SOC cohort, and S_IRE_ is the median overall survival time for the IRE cohort. For the secondary efficacy analysis, the null hypothesis for PFS is H_0_: μ_soc_ = μ_IRE_ with the alternative hypothesis being H_1_: μ_soc_ ≠ μ_IRE_, where μ_soc_ is the median PFS time for the SOC cohort, and μ_IRE_ is the median PFS time for the IRE arm. The null hypothesis for each state that there is no difference in median OS or PFS time post the initial 3 months of therapy between the IRE cohort and the SOC cohort, while the alternative hypothesis states there is. This study is powered to show the superiority of OS and PFS in the IRE cohort over the SOC cohort. The above null hypotheses will be tested by a 2-sided log rank test stratified by propensity score quintiles at the 0.05 significance level. The PFS endpoint will be tested only if the result of testing the primary effectiveness endpoint is statistically significant. Exploratory subgroup analyses will include patient’s sex (male or female), and other factors to be determined after the study team reviews the final analyses of primary and secondary endpoints.

There will be one planned interim analysis for the registry study, to be conducted when 50% of 266 patients in either cohort die, or per the recommendation of the DMC. The purpose of the interim analysis is to examine accrual rate and check the assumptions about the median survival times (i.e., 12 months for SOC cohort and 18 months for the IRE cohort), to ensure that the study will have sufficient power for planned analyses.

Exploratory analyses for the registry study will include OS from date of diagnosis, PFS from date of diagnosis, chemotherapy-free days per 100 person-months of follow-up after enrollment, proportion of patients treated with opioids for cancer-related pain at 3, 6, 12, 18 and 24 months after enrollment, mean Morphine Milligram Equivalent (MME)/Day among patients using opioids in each cohort at these time points, rates of avoidable events associated with chemotherapy in the IRE arm during chemotherapy free days compared to the control arm, 30-day unplanned readmissions, in-hospital mortality and identification of risk factors and biomarkers associated with outcomes. These exploratory analyses will be descriptive and, as deemed necessary, will be stratified by propensity score quintiles, or including propensity scores as a covariate. Unless explicitly stated otherwise in the analysis plan, the exploratory analyses will be based on the Effectiveness population. The analysis method for OS from date of diagnosis and PFS from date of diagnosis will be the same as for OS from date of enrollment. Poisson regression model will be used for analyzing chemotherapy-free days, and logistic regression model will be used for analyzing other binary endpoints.

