A growing body of evidence exists on the use of the NanoKnife System to treat pancreatic tumors, including both borderline resectable and unresectable tumors [14–16]. Studies have reported a median OS from diagnosis ranging from 14 to 27 months [17–27] and a median OS from IRE treatment ranging from 10 to 27 months [28–30]. The largest of these studies, a 200-patient, multicenter registry of patients with stage 3 pancreatic cancer treated with IRE via an open surgical approach, reported a median OS of 24.9 months and a median local progression free interval of 10.7 months [21]. Holland et al. recently reported results from a multicenter registry which included 152 patients with LAPC treated with IRE via an open approach at 6 different institutions [31]. Median OS from diagnosis, progression-free survival (PFS), and time to progression (TTP), all from diagnosis were 30.7 months, 22.8 months, and 27.3 months, respectively.

Narayanan et al. reported a retrospective review of 50 patients with LAPC treated with percutaneous IRE (26). Median OS was 27 months (95% confidence interval [CI], 22.7–32.5 months from the time of diagnosis) and 14.2 months (95% CI, 9.7–16.2 months) from the time of IRE. Multivariate analysis demonstrated patients with tumors ≤3 cm had significantly longer median OS than patients with tumors > 3 cm (33.8 vs. 22.7 months from time of diagnosis; *p* = 0.002, and 16.2 vs. 9.9 months from time of IRE; *p* = 0.031). More recently, Ruarus et al. reported the results of the Phase II multicenter PANFIRE II study which prospectively enrolled 50 patients treated with CT-guided percutaneous IRE [25]. This included 40 patients with LAPC and 10 patients with local recurring pancreatic cancer following resection. The median OS from diagnosis for patients with LAPC was 17 months. For patients with local recurrence, the median OS was 16 months from the diagnosis of recurrence and 9 months from IRE treatment. He et al. retrospectively compared 36 patients treated with IRE and 40 patients receiving radiotherapy with both groups receiving 4 months of induction chemotherapy prior to treatment [32]. Following a Propensity Score Matching (PSM) analysis, patients in the IRE group had longer median OS than patients receiving radiotherapy (21.6 months vs. 10.6 months) with significantly greater 1-year (71.4% vs. 41.3%) and 2 year (53.5% vs. 20.7%) OS rates (*p* = 0.011).

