### Registry study

The registry study will enroll 266 patients in the IRE cohort and 266 patients in the SOC cohort in order to achieve 90% power for analyzing both the OS and PFS endpoints. The power calculation assumes that it will take 24 months for accrual, and all 532 patients will be followed for at least 3 months after completion of accrual. The sample size consideration was based on the assumptions that the median OS time will be 12 months for SOC cohort and 18 months for the IRE cohort and there will be a 0.05 Alpha level (Type I error rate). For the secondary effectiveness endpoint of PFS, 210 patients will be needed per cohort for 90% statistical power assuming a median PFS of 8 months and 12 months for the SOC and IRE cohorts, respectively, or 116 patients per cohort if the median PFS survival is 8 months for the SOC cohort and 14 months for the IRE cohort.

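### The registry's confirmatory test adjusts through five propensity strata only, so measured confounding can remain within strata; depending on its assumed strength, false IRE benefit runs from about nominal to about 2.4 times nominal

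*Protocol article*

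**What the plan says.** In the protocol article, Statistical analysis, Registry study, the confirmatory rule for OS and PFS is: "The above null hypotheses will be tested by a 2-sided log rank test stratified by propensity score quintiles at the 0.05 significance level". PFS is gated: "The PFS endpoint will be tested only if the result of testing the primary effectiveness endpoint is statistically significant". The analysis set is "an Effectiveness Population which consists of all enrolled patients who will be matched by propensity score quintiles". This matching is by quintile, so it adds nothing finer than the five strata.

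The continuous score appears once, in the paragraph on exploratory analyses of the same section: "These exploratory analyses will be descriptive and, as deemed necessary, will be stratified by propensity score quintiles, or including propensity scores as a covariate". No within-stratum adjustment is stated for the primary test.

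On size, Sample size and statistical considerations, Registry study, says: "The registry study will enroll 266 patients in the IRE cohort and 266 patients in the SOC cohort in order to achieve 90% power" for OS and PFS, and "The power calculation assumes that it will take 24 months for accrual, and all 532 patients will be followed for at least 3 months" after accrual ends. The abstract instead gives at least 24 months of follow-up for the registry, so both durations are examined below.

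**The concern.** Five strata are a coarse form of adjustment. Inside a stratum, chiefly the lowest and the highest, patients who received IRE tend to have higher scores than those who did not. If the score is related to prognosis, a difference in prognosis between cohorts survives within the stratum even when every confounder has been measured and the score model is correct.

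Selection toward IRE is plausible here. Table 1 requires IRE-site patients to be judged eligible for the ablation and to receive it. Key eligibility criteria admits patients who choose IRE over randomization. The Background reports tumor size as prognostic after IRE ("16.2 vs. 9.9 months from time of IRE" for smaller against larger tumors).

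The residual bias does not shrink as deaths accumulate, whereas the standard error does. At stake is whether a significant registry result can be taken at its stated level. The registry is described as powered to show superiority, and the Discussion says positive results would support standard use of IRE.

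**Working it through.** **1. Reproduce the plan's figure.** Inputs from Sample size, Registry study: medians 12 and 18 months (HR 12/18 = 0.667 if exponential), two-sided 0.05, 90% power, 24 months' accrual, 3 months' minimum follow-up.

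- Events (Schoenfeld): 4(1.960 + 1.282)²/(ln 1.5)² = 42.03/0.1644, about 256.
- Event probability with uniform accrual: 1 − [exp(−3λ) − exp(−27λ)]/(24λ). SOC, λ = ln2/12: 0.545. IRE, λ = ln2/18: 0.419.
- Per cohort: 256/(0.545 + 0.419), about 266. Power at 266 is 90.1%. The stated figure is reproduced, but it describes an unconfounded comparison.

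**2. False-benefit rate when IRE does nothing.** From the plan: 266 + 266 patients and the quintile-stratified log-rank test, with benefit declared at Z < −1.96 (nominal 2.5%). Assumed, because the article gives neither: the standardized difference (SMD) between cohorts on one confounder score, and the hazard ratio per SD of that score. Also assumed: the score is fully aligned with prognosis, selection favors IRE, and the propensity model is correct and estimated from the data. There were 10,000 runs per row (Monte Carlo SE about 0.16 points), with 3 months' follow-up.

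| SMD | HR per SD | OS, false benefit | Ratio to 2.5% | OS, two-sided error | PFS median (8 months) tested alone | Ratio | OS, no adjustment |
|---|---|---|---|---|---|---|---|
| 0.25 | 0.80 | 2.6% | 1.04 | 4.9% | 2.5% | 1.00 | 6.8% |
| 0.50 | 0.80 | 2.9% | 1.15 | 4.8% | 3.1% | 1.24 | 14.5% |
| 0.50 | 0.67 | 3.4% | 1.38 | 5.2% | 3.7% | 1.48 | 36.2% |
| 0.75 | 0.67 | 3.9% | 1.56 | 5.4% | 3.9% | 1.56 | 67.5% |
| 1.00 | 0.67 | 4.0% | 1.60 | 5.5% | 4.9% | 1.95 | 89.3% |
| 1.00 | 0.50 | 5.7% | 2.28 | 6.6% | 5.9% | 2.37 | 100% |

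The quintiles remove most of the bias but not all of it.

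**3. Check by normal approximation.** The mean Z in the OS rows runs from −0.05 to −0.39. Φ(−1.96 + 0.39) = 5.8%, against 5.7% simulated. With about 532 × 0.545 = 290 deaths, the SE is roughly 2/√290 = 0.117. The null HR is then about exp(−0.39 × 0.117) = 0.96 at worst and exp(−0.05 × 0.117) = 0.99 at best. Separate simulations gave 0.95 to 0.99.

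**4. Longer follow-up.** With 24 months' minimum follow-up the event probability at a 12-month median is 0.865, so about 460 deaths. The same bias gives a Z larger by √(460/290) = 1.26: 0.39 × 1.26 = 0.49, and Φ(−1.96 + 0.49) = 7.1%. The simulated figure for that row was 7.7% (3.1 times nominal; 1,500 runs), with a two-sided error of 7.7% + 0.7% = 8.4%.

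**5. Weaker alignment.** With eight covariates and a correlation of 0.5 between propensity and prognosis, the ratio at 3 months was 0.9 to 1.6, and between 0.9 and 1.3 in four of five scenarios (1,500 runs each, SE about 0.4 points).

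**6. Remedy.**

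- Adding the score as a linear covariate within quintiles gave 2.3% to 3.2% false benefit in the single-score, 3-month scenarios (1,500 runs each). With eight fully aligned covariates it gave 1.3% to 3.8%.
- Adding the logit score gave 2.3% to 2.5% in an 8,000-run set-up. In a 1,500-run set-up that included prognosis not linear in the score, it gave 1.5% to 2.3%, where quintiles alone gave 2.7% to 5.5%. The null HR was about 1.00 in both, and in the second the SE rose by about 1%.

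**7. Power.** At HR 0.667 in a middle scenario, power was 87.6% with quintiles alone and 82.5% with the logit score. In Z units, 1.155 − 0.935 = 0.22. A 1% larger SE explains 3.115 × (1 − 1/1.01) = 0.03 of this, where 3.115 = 1.96 + 1.155. The other 0.19, multiplied by an SE near 2/√256 = 0.125, is a log hazard ratio of 0.024, or HR 0.976. That lies inside the null-bias range in step 3.

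**The case against.** A reader might infer that this test inflates false benefit by a fixed factor, such as 1.4 to 2.4, so that the 0.05 level is simply not held. The documents do not support that. They give no covariate list, no expected imbalance and no prognostic strength, and the upper ratios need strong confounding fully aligned with prognosis. The rates in step 2 start at nominal.

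The one prognostic contrast available is weak support. ln(16.2/9.9) = 0.49; if 3 cm were the median of a normal distribution, the halves would lie about 1.6 SD apart, giving 0.31 per SD, or HR 0.73. That median is not stated, the source is a 50-patient retrospective review, and Table 1 caps registry tumors at 3.5 cm. Taken at face value, it points to the table's 0.80 and 0.67 rows and not to the last row.

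Other counterpoints also stand:

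- Control sites without the device are to be chosen as comparable (Methods, Registry study), and Table 1 restricts ECOG status and progression. Both narrow differences, although site comparability does not match tumor size or fitness.
- Direction is assumed. Reversed selection would inflate false harm instead.
- Because PFS is gated, when IRE affects neither endpoint a false PFS claim cannot be more frequent than a false OS claim.
- Quintile stratification is an accepted method, and the Discussion concedes that non-randomized comparisons are weak.

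What does not stand is that this is merely detail left to an analysis plan. The article states the test. An unseen plan could add the score only by changing that test, and the article confines the covariate option to exploratory work.

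**Conclusion.** The point holds as a conditional risk. The stated confirmatory test leaves within-stratum confounding by factors the propensity score already measures. The assumptions are no IRE effect, 266 per cohort, 3 months' minimum follow-up and better-prognosis patients selected for IRE. Under them, the OS false-benefit rate is about 2.6% to 5.7% against 2.5%. That is 1.0 to 2.3 times nominal, with up to 2.4 times at the PFS median if PFS were tested alone. On the plan's own two-sided scale, error is about 5% to 7% instead of 5%. The null hazard ratio of about 0.95 to 0.99 is small beside the planned 0.667. With 24 months' follow-up the most extreme setting reached 3.1 times. With weak or partly aligned confounding there is little or no inflation. This is an inexpensive improvement to a confirmatory test, and it does not show that the registry result would be invalid. Unmeasured confounding is a separate matter that neither version of the test addresses.

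**What to change.** Keep the propensity quintiles as strata. Make the primary test for OS, and for PFS in its gated place, the cohort term in a Cox model stratified by quintile with the continuous logit propensity score as a covariate, two-sided at 0.05. Report the quintile-stratified log-rank test as supportive.

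The cost is a change of wording, one model term and about a 1% larger standard error. The sample size formula is unchanged. Apparent power falls (about 83% instead of 88% in the middle scenario), but almost all of that gap is bias being removed. The stated 90% should be read as the power of an unconfounded, unadjusted comparison. The remedy returns the error to near nominal in most simulated settings, though not exactly in all, and it depends on a reasonable score model.

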#### Study endpoints and assessments

The primary efficacy endpoint for both the RCT and the registry study will be OS defined as the time (in months) from randomization or enrollment in the registry to the date of death for any reason. Co-primary safety endpoints include time (in months) from randomization or enrollment in the registry to death or new onset of Grade 4 AE, and the development of high-grade complications defined as any AE or SAE with a CTCAE v5.0 grade of 3 or higher.

Secondary endpoints for both studies include a) PFS defined as the time (in months) from randomization or enrollment in the registry to the date of first observed disease progression (per clinical and radiologic criteria), or death from any cause, if death occurs without documented disease progression, b) procedure-related pain in subjects in the IRE arm, as measured by the Brief Pain Inventory (BPI-SHORT FORM) on the day of the procedure and post-procedure days 1, 7, 14 and 30, c) cancer-related pain assessed in the control and IRE arms using the BPI-SHORT FORM at baseline, 3 months, 6 months and at 6-month intervals thereafter, and d) QOL assessed in the control and IRE arms using the EQ-5D questionnaire at baseline, 3 months, 6 months and then at 6-month intervals for the duration of the study.

The registry study will also assess several exploratory endpoints including chemotherapy-free days (after 3 months of SOC), the need for opioids for cancer-related pain, OS from date of pancreatic cancer diagnosis, PFS from date of enrollment, and identification of risk factors and biomarkers associated with outcomes. Additional QOL exploratory endpoints which will be collected include rates of avoidable events associate with chemotherapy in the IRE arm during chemotherapy free days compared to the control arm, unplanned readmissions within 30 days following discharge, and in-hospital mortality.

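### The registry's avoidable-events comparison limits the IRE cohort, but not the control cohort, to time off chemotherapy, which favours IRE even with no effect

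*Protocol article*

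**What the plan says.** The comparison appears twice in the protocol article, in nearly the same words. Study endpoints and assessments lists it among the registry's additional exploratory quality-of-life endpoints: "rates of avoidable events associate with chemotherapy in the IRE arm during chemotherapy free days compared to the control arm". The Registry study part of Statistical analysis repeats it: "rates of avoidable events associated with chemotherapy in the IRE arm during chemotherapy free days compared to the control arm". In both places the time restriction follows the IRE arm, and the control arm is named without one.

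Three other statements bear on the point:

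- The Registry study part of Methods describes the IRE cohort as receiving IRE on top of standard of care. The Background says that standard of care includes systemic chemotherapy. IRE patients can therefore have chemotherapy days after enrollment, and control patients can have days without chemotherapy.
- Time off chemotherapy is an outcome in its own right, reported as "chemotherapy-free days per 100 person-months of follow-up after enrollment".
- On status and adjustment, the plan says: "These exploratory analyses will be descriptive and, as deemed necessary, will be stratified by propensity score quintiles, or including propensity scores as a covariate".

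**The concern.** An event tied to chemotherapy should be more frequent on or near chemotherapy than away from it. If one cohort is observed only off chemotherapy and the other over all its time, the two rates describe different kinds of time. The difference between them mixes any effect of IRE with the plain contrast between being on and off chemotherapy, and that contrast runs in IRE's favour.

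Propensity scores do not help. They balance patient characteristics at entry and cannot make unequal observation windows equal.

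At stake is how one exploratory registry result is read. A lower rate in the IRE cohort could be taken as evidence that IRE spares patients chemotherapy-related harm when the definition alone would produce it.

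**Working it through.** The article gives no event rate, count or power for avoidable events, so there is no figure of the plan's own to reproduce. The check asks what the stated comparison would show if IRE had no effect.

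**Inputs**

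- From the article: IRE events are counted during chemotherapy-free time, and no window is stated for control.
- Assumed: the rate is events per person-time, and control time is all follow-up.
- Assumed: q, the share of follow-up on chemotherapy, equal in both cohorts. Values 0.25, 0.50 and 0.75.
- Assumed: k, the event rate on chemotherapy divided by the rate off it. Values 1, 2, 3, 5 and 10.

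**Formulas.** Let r be the off-chemotherapy event rate, the same in both cohorts under no effect.

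- IRE, chemotherapy-free time only: r
- Control, all time: q·k·r + (1−q)·r = r(qk + 1 − q)
- Apparent rate ratio, IRE to control: 1/(qk + 1 − q)

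**Worked examples**

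- q=0.25, k=2: 1/(0.50 + 0.75) = 1/1.25 = 0.80
- q=0.50, k=5: 1/(2.50 + 0.50) = 1/3.00 = 0.33

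**Apparent rate ratio with no true effect**

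| k | q=0.25 | q=0.50 | q=0.75 |
|---|---|---|---|
| 1 | 1.00 | 1.00 | 1.00 |
| 2 | 0.80 | 0.67 | 0.57 |
| 3 | 0.67 | 0.50 | 0.40 |
| 5 | 0.50 | 0.33 | 0.25 |
| 10 | 0.31 | 0.18 | 0.13 |

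The ratio is below 1 whenever k exceeds 1 and q exceeds 0. It equals 1 when k=1, which is not what one expects of events defined by their link to chemotherapy.

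**Can it hide harm?** Suppose IRE truly raises the event rate 1.5-fold, on and off chemotherapy alike. At q=0.50 and k=3 the comparison shows 1.5 × 0.50 = 0.75, an apparent benefit.

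**With matching windows.** If both cohorts use all follow-up, the ratio under no effect is r(qk+1−q)/r(qk+1−q) = 1.00. If both use chemotherapy-free time only, it is r/r = 1.00. Both hold for every q and k.

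**The case against.** The strongest reply is that this is one item in a list, in an article that condenses two protocols. It defines neither an avoidable event nor a denominator nor the time at risk, and such detail commonly sits in the full plan. That controls are counted over all follow-up is inferred from silence, and a shared chemotherapy-free window may have been meant. This stands as a limit on certainty. It does not remove the point: the article does state the contrast, states it one-sidedly, and does so in both the endpoint and the analysis sections.

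A second reply is that a rate need not be per person-time. The analysis section names Poisson regression for chemotherapy-free days and logistic regression for other binary endpoints, and it assigns no model to this item by name. That also stands, and on another reading the formula would not apply. The direction is less sensitive. If the measure were the proportion of patients with an event, dropping part of one cohort's time could only lower that cohort's proportion or leave it unchanged.

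Third, the analysis is exploratory and descriptive. This is correct and limits the consequence. A reader might infer that the registry's pain and quality-of-life aims are compromised. They are not: those secondary endpoints use the Brief Pain Inventory and EQ-5D in both arms on a common schedule.

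A reader might also infer a similar fault in the opioid-dose measure, "mean Morphine Milligram Equivalent (MME)/Day among patients using opioids in each cohort at these time points". The documents do not support that. The users-only rule is the same in both cohorts, so it creates no difference when IRE has no effect. If IRE changes who uses opioids, the two user groups cease to be comparable, but the bias has no fixed direction. The plan also reports the "proportion of patients treated with opioids for cancer-related pain at 3, 6, 12, 18 and 24 months after enrollment" alongside it. Take an example in which half of patients use 20 and half use 100 MME/day, and IRE takes the first half off opioids. The users-only mean rises from 60 to 100, but the proportion using opioids falls from 100% to 50%. Multiplying the two gives the all-patient mean, 60 before and 0.5 × 100 = 50 after, provided both measures cover the same patients and the same opioid use.

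**Conclusion.** The point holds for the avoidable-events comparison. As worded in both sections, it excludes on-chemotherapy time from the IRE cohort only, and it favours IRE under no effect whenever events are more frequent on chemotherapy.

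The direction follows from the literal wording. The size does not come from the documents. It rests on a person-time rate, on control time being all follow-up, and on assumed values of q and k. Over the grid with k from 2 to 10 the apparent ratio runs from 0.80 down to 0.13. These values show how sensitive the measure is; they do not estimate the bias in this registry, and no single percentage should be attached to it.

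The consequence is minor. One exploratory, descriptive registry endpoint is affected. The sample size, the testing order for overall and progression-free survival, the co-primary safety endpoints and the randomized trial are untouched. The opioid-dose measure is not an error.

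**What to change.** Reword the item in both sections so that one time window applies to both cohorts:

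- **Main comparison:** avoidable chemotherapy-associated events per person-time over all follow-up from enrollment, in both cohorts. If IRE leads to fewer chemotherapy days, this comparison captures that as part of any benefit.
- **If a chemotherapy-free view is kept:** restrict both cohorts to chemotherapy-free days and label the result descriptive. Time off chemotherapy arises after enrollment and may itself differ by cohort.

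If a shared window was already intended, saying so for the control cohort is enough for that second view.

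As an optional supplement only, mean MME/day could also be shown over all patients assessed at each time point, with non-users counted as 0.

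The cost is wording. Chemotherapy-free days and avoidable-event rates are already planned endpoints, so the data needed should be at hand. No sample size or confirmatory test changes.

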### Registry study

The multicenter, observational registry study will include patients with Stage 3 PDAC who received SOC alone and those treated with IRE in addition to SOC (Fig. 2). Both cohorts will be required to undergo at least 3 months of SOC without progression prior to enrollment in the registry. The accrual time for the registry study is 24 months, and each patient will be followed-up for at least 3 months after the study enrolls 266 patients in each cohort. The Registry study will enroll both control and IRE patients from sites where patients are routinely treated with ablation using the NanoKnife System. Additional control patients will also be enrolled from sites that do not offer treatment with the NanoKnife System. The non-NanoKnife sites will be selected to be comparable to the NanoKnife sites with respect to type of center, geography, size, volume of patients with pancreatic cancer, volume of pancreatic cancer surgeries, type of chemotherapy, and duration of chemotherapy.

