*Randomized Controlled Multicenter Study* ● Signed and dated informed consent form. ● 18 years of age and older. ● Diagnosis of unresectable Stage 3 pancreatic adenocarcinoma cancer cytologically or pathologically confirmed per American Joint Committee on Cancer (AJCC) staging criteria. ● Tumor evaluated as Stage 3 according to National Comprehensive Cancer Network (NCCN) guidelines, based on radiographic imaging or exploratory surgery. ● Maximum axial and anterior to posterior tumor dimension of ≤3.5 cm, after receiving three months of treatment with the mFOLFIRINOX regimen. ● Has received 3 months of treatment with the mFOLFIRINOX regimen. ● Has an Eastern Cooperative Oncology Group (ECOG) performance status of 0 or 1. ● Has an American Society of Anesthesiologists (ASA) classification of physical health status of 1, 2, 3 or 4.	*Multicenter Registry* ● Signed and dated informed consent form ● 18 years of age and older ● Diagnosis of Stage 3 PC cytologically or pathologically confirmed per American Joint Committee on Cancer (AJCC) staging criteria. ● Tumor evaluated as Stage 3 according to National Comprehensive Cancer Network (NCCN) guidelines, based on radiographic imaging or exploratory surgery ● Maximum axial and anterior to posterior tumor dimension of ≤3.5 cm after standard of care. ● Has received 3 months of standard of care per each participating institution’s guidelines ● Has an Eastern Cooperative Oncology Group (ECOG) performance status of 0 or 1. ● Has an American Society of Anesthesiologists (ASA) classification of physical health status of 1, 2, 3 or 4. ● Are at an IRE site and are deemed eligible for IRE and receive ablation using the NanoKnife System. ● Shows no evidence of disease progression based on NCCN guidelines after completing 3 months of standard of care.
Key Exclusion Criteria	

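### Registry OS and PFS from diagnosis are to be analysed as if patients were under observation from diagnosis; without delayed entry the cohort comparison is biased whenever the diagnosis-to-enrollment intervals differ

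*Protocol article*

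**What the plan says.** The registry's main OS endpoint starts at entry. Study endpoints and assessments has "OS defined as the time (in months) from randomization or enrollment in the registry to the date of death for any reason". Statistical analysis, Registry study, fixes the test for OS and for PFS: "The above null hypotheses will be tested by a 2-sided log rank test stratified by propensity score quintiles at the 0.05 significance level".

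The same section then adds OS and PFS from diagnosis as exploratory analyses. Of the exploratory set in general it says: "These exploratory analyses will be descriptive and, as deemed necessary, will be stratified by propensity score quintiles". For these two endpoints it is more specific: "The analysis method for OS from date of diagnosis and PFS from date of diagnosis will be the same as for OS from date of" registry entry.

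Entry is conditional. Methods, Registry study: "Both cohorts will be required to undergo at least 3 months of SOC without progression prior to enrollment in the registry". Table 1 adds a condition for the IRE cohort: "Are at an IRE site and are deemed eligible for IRE and receive ablation using the NanoKnife System". The article sets no upper limit on the time from diagnosis to enrollment, does not give that time by cohort, and does not say that it enters the propensity score.

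**The concern.** When the clock starts at enrollment, time zero and the start of observation coincide, and an ordinary log-rank test has the right risk sets. When the clock starts at diagnosis they do not coincide. Someone who died or progressed before enrollment is not in the registry, so each enrolled patient brings a stretch of time in which no event could have been recorded. Carrying the enrollment method over puts that stretch into the risk set.

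If the stretch has the same length in both cohorts, it cancels in the comparison. If one cohort has the longer stretch, its patients sit in the risk set without being able to have an event while patients in the other cohort are already dying. The test reads this as a treatment difference.

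At stake is how the from-diagnosis results are read. Several of the IRE results cited in the Background are given from diagnosis, so readers may set these registry figures beside them.

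**Working it through.** **1. The plan's own figure.** Sample size, Registry study: medians 12 and 18 months, alpha 0.05, 90% power, 24 months of accrual plus 3 months of follow-up.

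- Events (Schoenfeld): 4 × (1.960 + 1.282)² / (ln(12/18))² = 255.7, so 256.
- Event probability with rate λ = ln 2 / median: 1 − (e^(−3λ) − e^(−27λ)) / (24λ) = 0.545 (SOC) and 0.419 (IRE), mean 0.482.
- 256 / 0.4818 = 531.3, or 266 per cohort.

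The stated 266 per cohort is reproduced. It rests on OS from enrollment and is not touched by this point.

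**2. Size of the bias by hand.** Assumptions: no treatment effect, median OS 12 months from enrollment in both cohorts, 266 per cohort, constant hazard, accrual and follow-up as planned. The gap lengths are also assumed, because the article gives none: 4 months for SOC and 4 + g for IRE.

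For g months (from month 4 to month 4 + g after diagnosis) only SOC patients can die, while all 266 IRE patients are counted at risk. Take g = 2:

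- SOC deaths in the window: 266 × (1 − 2^(−2/12)) = 266 × 0.109 = 29.0.
- Average IRE share of the risk set: 266 / (266 + 251.5) = 0.514.
- IRE observed minus expected: 0 − 29.0 × 0.514 = −14.9. After the window the hazards are equal and add nothing on average.
- Total deaths: 532 × 0.545 = 290. Log-rank variance about 290/4 = 72.5.
- Apparent HR about exp(−14.9/72.5) = 0.81. Mean z about −14.9/√72.5 = −1.75. Rejection about Φ(−1.96 + 1.75) = 42%.

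**3. Simulation of the same setting** (2,000 registries per row, fixed gaps, unstratified, OS):

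| IRE gap minus SOC gap | HR, ordinary log-rank/Cox from diagnosis | Rejection | HR, delayed entry | Rejection |
|---|---|---|---|---|
| 0 | 1.00 | 5.1% | 1.00 | 5.1% |
| 1 month | 0.90 | 15.5% | 1.00 | 5.8% |
| 2 months | 0.81 | 42.6% | 1.00 | 4.4% |
| 3 months | 0.74 | 73.5% | 1.00 | 4.9% |
| 4 months | 0.66 | 94.4% | 1.00 | 4.9% |
| −2 months (SOC longer) | 1.23 | 43.0%, none favouring IRE | 1.00 | 4.1% |

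A 4-month difference alone gives about the planned effect, 12/18 = 0.667.

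**4. Sensitivity.**

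- Other gap distributions: differences of 1, 2 and 3 months give HR 0.90–0.91, 0.81–0.83 and 0.74–0.75, with 12–16%, 39–43% and 70–74% rejection.
- Follow-up of 24 months after accrual (the Abstract gives at least 24 months for every patient, the registry sections at least 3 months after accrual): HR about 0.94, 0.89 and 0.83, with about 11%, 25% and 50% rejection.
- Stratifying by quintiles of a prognostic score that leaves out the gap (600 registries per scenario): HR 0.90, 0.82 and 0.72, with 13%, 34% and 74%. Stratification of that kind does not remove the bias.
- PFS, median 8 months in both cohorts: differences of 2 and 3 months give HR 0.78 and 0.69, with 65% and 93%.

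**5. Medians.** With equal mean gaps of 4 months, the ordinary Kaplan-Meier median from diagnosis is about 16 months and the delayed-entry median 15.0. With identical hazards and mean gaps of 4, 7 and 10 months, delayed-entry medians are 15.0, 16.9 and 19.8 months. Delayed entry therefore repairs the log-rank and Cox comparison but not the comparison of medians. It is also unstable: at a mean gap of 7 months, the 5th to 95th percentile range of the median is 6.8–19.2 months, against 17.2–21.1 for the ordinary curve.

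**The case against.** **Exploratory status.** These analyses are called descriptive and carry no alpha. The confirmatory sequence is OS and then PFS, both from enrollment. This stands: the rejection rates above measure how misleading the comparison could be, not a loss of the registry's type I error. A reader might infer that the primary result is at risk; nothing here supports that.

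**The longer IRE gap is not in the document.** This also stands. Both cohorts face the same 3-month rule. Sites without the device are to be comparable in duration of chemotherapy. Patients who prefer IRE to randomization may enter soon after induction. It is tempting to conclude that the error must favour IRE, on the strength of the percutaneous series in the Background: "Median OS was 27 months (95% confidence interval [CI], 22.7–32.5 months from the time of diagnosis) and 14.2 months (95% CI, 9.7–16.2 months) from" ablation. But 27 − 14.2 = 12.8 months is a difference of two medians in one retrospective series of 50 patients, not a measured gap, and the article does not say that series used the registry's entry rule. It shows only that the interval can be long. Setting it against the 3-month minimum for SOC would compare an observed figure with a floor that applies to both cohorts.

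**Inflated medians.** A reader might also infer that survival is overstated by the whole gap, for instance that a 12-month median becomes 16, or 33% too long. Most of that is the change of origin: the pre-enrollment months were lived. The ordinary and delayed-entry medians differ by about 1 month (16 against 15.0).

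**Analysis-plan detail.** Risk-set coding and the propensity covariates may be in a plan not shown, and a delayed-entry log-rank is still a stratified log-rank. This has some force. But the article does not leave the method open: it prescribes the enrollment-origin method, which needs no entry time, for endpoints that do need one.

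**Conclusion.** The point holds in conditional form. The article carries a method that is valid from enrollment over to left-truncated data from diagnosis. The between-cohort comparison is then biased toward whichever cohort has the longer diagnosis-to-enrollment interval, and by a material amount once the intervals differ by 2 or 3 months.

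The figures rest on assumed gaps, constant hazards and a gap unrelated to later survival. That last assumption is also what lets delayed entry perform so cleanly in the simulation. The two cohorts enter by different routes, so unequal intervals are plausible, but neither their size nor their direction is known. The consequence is confined to two exploratory endpoints. It is worth correcting because the correction is cheap and a spurious hazard ratio of 0.7 to 0.8 could be read as support for the main analysis.

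**What to change.** In the exploratory-analysis paragraph of Statistical analysis, Registry study, replace the sentence on the from-diagnosis method with wording such as: *Between-cohort log-rank and Cox analyses of OS and PFS from diagnosis will use delayed entry, each patient joining the risk set at the enrollment date on the time-since-diagnosis scale, stratified by propensity score quintiles. The diagnosis-to-enrollment interval will be reported by cohort. Medians from diagnosis will be presented descriptively, as conditional on having reached enrollment, and will not be compared between cohorts.*

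The cost is this wording, an entry-time argument in the survival procedures and one extra table; both dates are needed for the planned analyses anyway. There are two downsides. Risk sets are small in the first months after diagnosis, so early estimates are unstable. Delayed entry also assumes that entry time is independent of later risk, and this should be stated with the results.
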